## Abstract

Reconstruction following extensive resection of tongue squamous cell carcinoma remains challenging because the optimal pedicled flap for 
achieving superior functional recovery and aesthetic outcomes is still uncertain. Therefore, it is of interest to compare pectoralis major 
myocutaneous (PMMC) and pectoralis major myofascial (PMMF) flaps for reconstruction of Type III and Type IV tongue defects in patients 
undergoing surgical treatment for squamous cell carcinoma. Twenty-four eligible patients will be randomly allocated into two groups, and 
post-operative outcomes including flap-related complications, tongue shape, swallowing, speech and tongue mobility will be evaluated at 1 
week, 1 month and 3 months using standardized clinical assessment scales. Functional and aesthetic outcomes between the two reconstruction 
techniques will be analyzed using appropriate statistical methods to determine differences in clinical performance and patient rehabilitation. 
Thus, data shows to generate evidence that supports selection of the most effective pedicled flap for tongue reconstruction and improves 
functional recovery, quality of life and clinical decision-making in resource-constrained settings.

## Background:

Oral cancer remains a major health burden in India, ranking among the most common malignancies and being reported in nearly 25% of cancer 
registries. Alarmingly, about 80% of cases are diagnosed at advanced stages, limiting survival [1]. 
GLOBOCAN data indicate that India contributes to one-third of global oral cancer cases, with oral cancer accounting for approximately 30% 
of all cancers nationally. ICMR reports show that men are disproportionately affected, largely due to tobacco and alcohol use [2]. 
Tongue squamous cell carcinoma (TSCC) constitutes nearly 45% of oral cavity cancers [3], with an 
increasing prevalence among younger individuals [4, 5, 
6, 7]. Its aggressive biology, early metastasis and poor 
prognosis emphasize the need for timely diagnosis, effective therapies and reconstruction to improve survival and quality of life. Enhancing 
therapeutic approaches tailored to younger patients may help improve their prognosis and overall survival rates. With the increasing burden 
of TSCC, particularly among young individuals, prioritizing research and clinical advancements in this area is essential for better 
management and outcomes [8]. The tongue, an essential organ within the oral cavity and oropharynx, 
is a complex muscular structure covered by a thick mucous membrane. Although primarily responsible for taste perception, the tongue also 
plays a crucial role in mastication, deglutition, articulation and oral hygiene. It is innervated by five cranial nerves, which contribute 
to its diverse functions. The tongue is divided into the tip, body and base, with complex innervation supporting its functions [9]. 
Tobacco use remains the most significant risk factor for developing squamous cell carcinoma of the tongue, with smoking and smokeless 
tobacco products contributing to approximately 85% of head and neck cancers. Secondhand smoke exposure also increases the risk. Additionally, 
alcohol consumption is a notable factor, particularly when combined with tobacco, leading to a synergistic effect that exponentially 
increases the likelihood of cancer development [10]. Other contributing factors include poor oral 
hygiene, tooth loss and, potentially, the prolonged use of alcohol-based mouthwashes. Dietary habits influence oral cancer risk, with 
vitamin A, β-carotene and α-tocopherol offering protective effects [11]. Genetic 
predisposition also contributes, as inherited syndromes such as Fanconi anemia and dyskeratosis congenital impair DNA repair and increase 
the risk of malignancy, including oral cancers [12, 13, 14]. 
HPV's role in tongue cancer is less clearly defined than in oropharyngeal cancers, but established carcinogens, including tobacco, alcohol 
and betel nut, remains major factors, emphasizing the importance of preventive strategies [15]. Over 
90% of oral cancers do squamous cell carcinomas, highlighting the importance of risk assessment, understand pathogenesis and early 
detection for better outcomes. Surgical excision is the primary treatment but often causes significant tissue loss. Reconstruction using 
pedicled pectoralis major myocutaneous (PMMC) flaps or microvascular free tissue transfer is essential to restore function and aesthetics. 
The PMMC flap gained popularity because of its technical simplicity, reliability and close proximity to the head and neck region. Despite 
the earlier introduction of microvascular free flaps, they were not widely adopted because of the need for specialized training and 
infrastructure [16]. The selection of a reconstruction method depends on the defect size and follows 
the reconstructive ladder. In advanced OSCC cases, reconstructive options primarily include pedicled flaps and microvascular free flaps 
(MFFs). MFFs have revolutionized reconstruction by enabling the repair of complex oral cavity defects, significantly enhancing both 
function and appearance and thereby improving patient outcomes. However, MFFs carry the risk of flap failure due to factors such as 
inadequate surgical expertise, flaws in flap design and harvesting, vascular anastomosis issues and complications at irradiated donor sites.

Venous congestion (83%) and arterial compromise (8%) are common complications. Additionally, MFFs may not always be feasible because of 
financial constraints or limited healthcare resources [17]. Pedicled flaps, such as the pectoralis 
major myocutaneous (PMMC) flap, remain a reliable option for oral cavity reconstruction because of their ease of harvest, accessibility and 
relatively low failure rates. They are particularly valuable in high-volume centers with long surgical waiting lists. However, in female 
patients with advanced OSCC, bulky breast tissue and breast contour deformities may limit their application, making the pectoralis major 
myofascial (PMMF) flap a practical alternative for large oral cavity defects [18]. One major drawback 
of the PMMC flap is its bulk, which is influenced by the subcutaneous fat overlying the muscle and can hinder speech and swallowing 
rehabilitation, especially in anterior oral cavity and pharyngeal sites. This issue is more problematic in female or broad-chested patients 
and complications may be worsened when the mandible is preserved. Other limitations include intraoral hair growth, chest wall deformities 
and technical challenges with pedicle rotation. The PMMF flap, consisting of the pectoralis muscle and fascia without a skin island, addresses 
many of these drawbacks and has been reported as a versatile reconstructive option, although it remains underrepresented in the literature 
[19]. Partial hypopharyngeal defects following total laryngectomy (TLE) also pose reconstructive 
challenges. Loss of speech, impaired swallowing and complications such as fistulas, especially in previously irradiated patients, demand 
tailored approaches to optimize outcomes. While many techniques use free or regional flaps to create a cutaneous lining, the PMMC flap has 
lost favor because of its bulk and poor pliability. To overcome these issues, Robertson and Robinson introduced the PMMF flap in the 1980s, 
reducing complications. However, comparative evidence between PMMC and PMMF flaps remains limited [20]. 
Our study evaluates the post-operative outcomes of both flaps in tongue reconstruction. Most reconstructive techniques involve inverting a 
myocutaneous or fasciocutaneous free flap onto the remaining pharyngeal mucosa, forming a cutaneous lining. Historically, the pectoralis 
major myocutaneous (PMMC) flap has been widely used, but its bulkiness, poor pliability and risk of complications have reduced its 
popularity. To address these issues, Robertson and Robinson proposed the pectoralis major myofascial (PMMF) flap in the 1980s, which 
eliminates the skin island and reduces complications. Despite promising results, comparative studies between PMMC and PMMF flaps remain 
limited [20]. Therefore, this study aims to compare and evaluate the functional and aesthetic 
outcomes of the Pectoralis Major Myocutaneous (PMMC) flap versus the Pectoralis Major Myofascial (PMMF) flap for Type III and Type IV 
tongue defect reconstruction in patients operated on for squamous cell carcinoma of the tongue. Oral squamous cell carcinoma (OSCC) 
represents a major health burden in India, accounting for a significant proportion of global head and neck cancer cases. Advanced-stage 
disease often requires extensive surgical excision followed by reconstruction to restore function and aesthetics. In many developing and 
resource-limited settings, microvascular free flap reconstruction may not be feasible because of financial limitations, lack of 
infrastructure and patient-related factors. Under such circumstances, pectoralis major myofascial (PMMF) and pectoralis major myocutaneous 
(PMMC) flaps serve as reliable alternatives for reconstruction. Studies have shown that PMMF flaps are associated with lower complication 
rates and provide satisfactory functional and cosmetic outcomes, particularly in female patients, in whom preservation of breast contour is 
important [17]. PMMC flaps, based on the thoracoacromial artery, continue to play a significant role 
in head and neck reconstruction because of their proximity to the operative site, technical simplicity and ability to reconstruct complex 
defects effectively. They are especially useful in economically disadvantaged and malnourished patients, offering high success rates despite 
moderate complication rates [21]. Although traditional pectoralis myocutaneous flaps may present 
drawbacks such as chest wall deformity, hair growth and excessive tissue bulk, the development of pectoralis myofascial flaps has helped 
overcome many of these limitations. By eliminating the skin paddle, these flaps provide reduced bulk, improved cosmetic outcomes and 
reliable healing, with successful epithelialization occurring within a short period, even in patients undergoing radiotherapy [22]. 
Tongue squamous cell carcinoma (TSCC) has traditionally been associated with older individuals with long-term tobacco exposure. However, 
recent evidence indicates an increasing incidence among younger patients without conventional risk factors, suggesting that TSCC in younger 
populations may represent a distinct biological entity. Most studies define younger patients as individuals below 40 years of age, with a 
slight male predominance. While tobacco use remains a major risk factor in older adults, more than half of younger patients with TSCC have 
no history of smoking or tobacco use, indicating the possible involvement of alternative etiological factors such as genetic predisposition, 
viral infections and lifestyle-related influences. These findings highlight the importance of further research to identify nontraditional 
risk factors and improve prevention and early diagnosis strategies for younger populations affected by TSCC [8]. 
Oral cavity and pharyngeal cancers continue to contribute significantly to the global cancer burden, with higher incidence rates reported 
in men than in women. Management of oral tongue cancer requires a multidisciplinary approach involving oncologists, speech therapists, 
rehabilitation specialists and psychological support to address the complex functional and aesthetic challenges associated with treatment 
[15]. In reconstructive management following ablative surgery for oral squamous cell carcinoma, both 
Pectoralis Major Myocutaneous (PMMC) flaps and free flaps have demonstrated comparable complication rates. Although free flaps offer 
superior versatility and functional outcomes, PMMC flaps remain a practical and cost-effective option in resource-limited settings, 
particularly where financial constraints, lack of microvascular facilities and patient comorbidities limit the use of free flap 
reconstruction. Therefore, PMMC reconstruction continues to maintain clinical relevance in developing healthcare systems [16]. 
Therefore, it is of interest to compare the functional and aesthetic outcomes of pectoralis major myocutaneous and pectoralis major 
myofascial flaps for reconstruction of Type III and Type IV tongue defects following surgical treatment of tongue squamous cell carcinoma.

## Materials and Methods:

The study will be a parallel group randomized trial. It will be conducting from February 2025 to September 2026. This clinical study will 
take place at the Department of Oral and Maxillofacial Surgery, Siddharth Gupta Memorial Cancer Hospital, Sawing, Wardha. The research will 
be carried out under the auspices of the Datta Meghe Institute of Higher Education and Research, Sawing, Wardha Institutional Ethics 
Committee (IEC) approval from Datta Meghe Institute of Higher Education and Research (DMIHER) (DU) has been obtained and the process will 
begin after explaining the detailed treatment protocol to the patients. A total of 24 patients will be assessed for biopsy-proven cases of 
SCC, with 12 patients meeting the criteria for the study.

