## Sample size calculation:

The sample size was calculated using Cochran's formula Considering a Z value of 1.96, a prevalence (P) of total flap necrosis reported 
as 2% (0.02) and a desired margin of error (e) of 8% (0.08), the formula was applied as:

n=z^2^(pq)/e^2^

n = 1.962 *0.02*(1-0.02)/0.08*0.08

= 11.76

Thus, a minimum of 12 patients were required for the study in each group (Total=12x2=24). The prevalence data were obtained from the 
study conducted by Milenovic *et al.* [22]. After diagnosis, patients will be divided 
into two groups by computer generated randomization and then alternatively select for the reconstruction with pectoralis major myocutaneous 
flap or pectoralis major myofascial flap.

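### Materials and Methods gives 12 eligible patients out of 24 assessed; the Abstract and the sample size section give 24 eligible patients, 12 per group

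*Protocol article*

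**What the plan says.** Three places in the protocol article speak to the number of patients.

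- **Materials and Methods.** One sentence begins "A total of 24 patients will be assessed for biopsy-proven cases of" and ends "SCC, with 12 patients meeting the criteria for the study". It does not say that the 12 is per group.
- **Sample size calculation.** After applying a single-proportion precision formula, the section concludes: "Thus, a minimum of 12 patients were required for the study in each group (Total=12x2=24".
- **Abstract.** "Twenty-four eligible patients will be randomly allocated into two groups, and" outcomes are then to be followed up.

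The design is given in Materials and Methods: "The study will be a parallel group randomized trial". There are two groups, and the 12 x 2 in the sample size section implies equal allocation.

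**The concern.** The figure 24 has two meanings. In Materials and Methods it counts patients assessed, of whom 12 qualify. In the Abstract it counts eligible patients who are randomised, and in the sample size section it is the total required. A patient needed in a treatment group must be an eligible one, so the last two agree with each other and conflict with the first by a factor of two (24 against 12).

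The number randomised tells the trial team when enrolment is complete. It also tells a later reader whether the trial reached its planned size. With the text as it stands, a report on 12 patients could be presented as complete under one section and as half-recruited under the others.

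**Working it through.** **Inputs, all from the protocol article**

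- z = 1.96 ("Considering a Z value of 1.96, a prevalence (P) of total flap necrosis reported")
- p = 0.02 and e = 0.08 ("as 2% (0.02) and a desired margin of error (e) of 8% (0.08), the formula was applied as")
- Formula: n = z² p (1 − p) / e²
- Stated result: 11.76, rounded up to 12 per group, 24 in total
- Materials and Methods: 24 assessed, 12 meeting the criteria

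**Step 1. Reproduce the stated sample size.**

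n = 1.96² × 0.02 × 0.98 / 0.08² = 3.8416 × 0.0196 / 0.0064 = 11.765

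Rounded up, this is 12 per group, and 2 × 12 = 24. The protocol's figures are reproduced.

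**Step 2. Set the three statements side by side.**

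| Section | Assessed | Eligible or required in total | Per group |
|---|---|---|---|
| Abstract | not stated | 24 | not stated |
| Sample size calculation | not stated | 24 (minimum) | 12 (minimum) |
| Materials and Methods | 24 | 12 | not stated |

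The ratio of the totals is 24 / 12 = 2. Two of the three places agree, and one of them is the section that derives the number.

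**Step 3. What 12 eligible patients would mean.**

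Assuming 1:1 allocation, 12 / 2 = 6 per arm. The protocol does not print this figure; it follows from the sentence only under that assumption.

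**Step 4. Size on the protocol's own criterion.**

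Half-width = 1.96 × √(0.02 × 0.98 / n)

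- n = 12: 1.96 × √(0.0196 / 12) = 0.0792, or 7.9 percentage points
- n = 6: 1.96 × √(0.0196 / 6) = 0.1120, or 11.2 percentage points

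Twelve per arm meets the stated 8-point margin; six per arm does not.

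**The case against.** The strongest reply is that the intended size is not really in doubt. The dedicated section derives 12, says it applies to each group and writes out the total. The Abstract independently gives 24 eligible patients. Materials and Methods uses the same two numbers, so the likeliest explanation is a missing *in each group*. This largely stands, and it is why the point is a wording correction.

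It does not clear the sentence, however. With those words added, the text would still describe the 24 as patients assessed, which implies that everyone assessed is eligible. The inclusion and exclusion criteria list grounds on which an assessed patient can fail, such as lesions small enough for primary closure, uncontrolled systemic disease or unwillingness to take part. The sentence needs rewording on either reading.

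A reader might also infer three stronger things, none of which the document supports:

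- *That the sample size was miscalculated.* It was not; Step 1 reproduces it. Whether a one-sample precision formula suits a two-arm comparison is a separate question.
- *That recruitment will stop after 24 patients have been assessed and half the required number analysed.* The sentence contains no rule for ending recruitment, and the next section calls 12 per group a minimum.
- *That a stated level of power is lost.* The protocol gives no power target and no effect size. Any such figure would be the reader's own choice, and one based on a comparison of mean scores would bear on the secondary outcomes, not on the complications named as primary.

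**Conclusion.** The protocol article contradicts itself on the number of eligible patients: 12 in Materials and Methods, 24 in the Abstract and in the sample size section. This is an inconsistency in reporting and not an arithmetic error. The weight of the text favours 24, with Materials and Methods as the outlier.

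The precision cost arises only if the outlier were followed. The half-width at a 2% proportion would then be 11.2 points and not 7.9, against a stated margin of 8. That comparison assumes equal allocation of 12 patients. It uses the protocol's own normal-approximation formula, which is rough for an event this rare (12 × 0.02 = 0.24 expected events per arm), so it shows only whether the stated criterion is met.

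The correction should be made. It is not critical, because the governing number can be recovered from the rest of the document.

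**What to change.** Replace the sentence in Materials and Methods with: *Recruitment continues until 24 eligible patients have been randomised, 12 per group.* Do not fix the number assessed in advance, since it depends on how many patients meet the criteria.

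The cost is one sentence. The required number of patients, the design and the analysis stay as the Abstract and the sample size section already have them.

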## Sample size calculation:

The sample size was calculated using Cochran's formula Considering a Z value of 1.96, a prevalence (P) of total flap necrosis reported 
as 2% (0.02) and a desired margin of error (e) of 8% (0.08), the formula was applied as:

n=z^2^(pq)/e^2^

n = 1.962 *0.02*(1-0.02)/0.08*0.08

= 11.76

Thus, a minimum of 12 patients were required for the study in each group (Total=12x2=24). The prevalence data were obtained from the 
study conducted by Milenovic *et al.* [22]. After diagnosis, patients will be divided 
into two groups by computer generated randomization and then alternatively select for the reconstruction with pectoralis major myocutaneous 
flap or pectoralis major myofascial flap.

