## Primary outcomes: 

Suture line leakage, Fistula, Flap discoloration and Donor site morbidity.

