## Conclusion:

We show that protocol compares PMMC and PMMF flaps for reconstruction of Type III and Type IV tongue defects after oncologic resection. 
The study is expected to identify the reconstruction technique that provides better functional recovery with fewer post-operative 
complications. The findings may strengthen evidence-based reconstructive planning and improve patient-centered outcomes in tongue squamous 
cell carcinoma surgery.

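### The sample size rests on a one-sample prevalence formula for total flap necrosis, which is not a listed outcome; it supports no between-flap comparison, and its 8% margin depends on an approximation that fails at 12 per arm

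*Protocol article*

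**What the plan says.** The section Materials and Methods gives the design: "The study will be a parallel group randomized trial". The section Sample size calculation then states: "The sample size was calculated using Cochran's formula". Its inputs follow: "Considering a Z value of 1.96, a prevalence (P) of total flap necrosis reported" as 2% in a cited study, "and a desired margin of error (e) of 8% (0.08), the formula was applied as" n = z²pq/e². The answer, 11.76, is rounded up and doubled: "Thus, a minimum of 12 patients were required for the study in each group (Total=12x2=24").

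The section Primary outcomes lists four complications: "Suture line leakage, Fistula, Flap discoloration and Donor site morbidity". The section Secondary outcomes lists flap shape and size, swallowing, speech and tongue mobility. Total flap necrosis is in neither list. The section Statistical analysis plans repeated measures ANOVA, unpaired t tests and chi-square tests, with p below 0.05 as the criterion.

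The Conclusion is comparative: "The study is expected to identify the reconstruction technique that provides better functional recovery with fewer post-operative" complications. The Abstract, Utility and Expected outcome sections make similar promises.

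**The concern.** Cochran's formula answers one question: how many people are needed to estimate a single proportion to within a given margin. It has no term for a second group, a target difference, a standard deviation or power. Applying it to one arm and multiplying by two does not turn it into a calculation for a comparison. It is also applied to an event that the trial does not list as an outcome, at a prevalence so low that the large-sample theory behind the formula does not hold at the n it returns.

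This is not detail that an article leaves to a fuller document. The section gives a complete calculation and says that 12 per group were required. That is the only justification for N in the article, and the comparative promises depend on it. A reader could take the 8% margin as the precision of the trial, and could take a non-significant complication comparison as evidence that the flaps perform alike, when the trial would miss all but extreme differences.

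**Working it through.** **Inputs from the article.** z = 1.96, p = 0.02, e = 0.08 and 12 per group (Sample size calculation); two parallel arms (Materials and Methods); significance at p < 0.05 (Statistical analysis). The article does not say whether tests are one- or two-sided; two-sided is assumed here.

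**1. The plan's own figure.** The printed 1.962 is read as 1.96².

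n = 1.96² × 0.02 × 0.98 / 0.08² = 11.76, rounded up to 12. This reproduces.

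Nominal half-width at n = 12: 1.96 × √(0.02 × 0.98 / 12) = 0.079, or 7.9%. By its own formula, the plan meets 8%.

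**2. Whether the approximation is valid.**
- Expected events per arm: 12 × 0.02 = 0.24.
- Nominal interval: 2% ± 7.9%, about −6% to +10%, so it includes impossible values.
- Chance of no event in one arm: 0.98¹² = 0.785. In all 24 patients: 0.98²⁴ = 0.616.
- The normal-approximation (Wald) interval computed from the data has width zero for 0/12 and half-width 15.6 points for 1/12. Summed over all possible counts at n = 12 and p = 0.02, it covers the true value 21.5% of the time instead of 95%.

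**3. Precision that 12 patients give (exact Clopper-Pearson, 95%).**
- 0/12: upper limit 1 − 0.025^(1/12) = 0.265, so 0 to 26.5%.
- 1/12: 0.2% to 38.5%.
- 0/24, both arms pooled: upper limit 1 − 0.025^(1/24) = 0.142, so 0 to 14.2%.
- For zero events to give an upper limit of 10% or less (2% + 8%), one arm needs 36 patients.

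**4. What 12 per arm can compare (two-sided 5%, no dropout, no multiplicity adjustment).** The article gives no target difference, complication rate or SD, so the rates below are illustrative assumptions. Power for proportions is the sum of the binomial probabilities of all 13 × 13 possible tables in which the test is significant.

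| Comparison | Uncorrected chi-square | Fisher |
|---|---|---|
| 80% power from 5% in one arm needs, in the other | about 53% | about 61% |
| Power for 10% vs 30% | 19.8% | 9.5% |

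Against 0/12 in one arm, Fisher's test needs at least 5/12 in the other (p = 0.037).

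For a score compared by t test (22 degrees of freedom, noncentrality d × √(12/2)), 80% power is reached at d = 1.20 SD. This is approximate, because Tables 1 to 4 are five-level ordinal scales. The article gives no SD, so it cannot be converted to scale points.

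**The case against.** The strongest defence is that the number is correctly computed. A reader might infer from the exact intervals that the authors made an arithmetic error, or that 12 per arm misses 8% by their own formula. The article does not support that: the formula returns 11.76, and the nominal half-width at n = 12 is 7.9%. The fault is in using a large-sample formula where 0.24 events are expected.

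A second defence is that this is a small feasibility study for which no power is claimed. No section says so. The number is presented as required by the formula, and the aims are comparative. For the same reason, feasibility cannot be supplied as the basis for N on the authors' behalf.

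Third, the Abstract speaks broadly of flap-related complications, which could take in necrosis, and flap discoloration is a neighbouring item. What stands is narrower than saying that necrosis will never be recorded: total flap necrosis is absent from the stated primary and secondary outcome lists.

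Fourth, the article plans no equivalence claim, so misreading a null result is a risk in interpretation, not something the plan states. That is fair, and it limits the consequence. It does not rescue the justification for N.

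**Conclusion.** The point holds and should be corrected before the trial is reported. N for a two-arm randomized comparison is taken from a one-sample precision formula for an event outside the listed outcomes, and nothing in the calculation bears on a difference between the flaps. The 8% margin is a nominal output of the formula, not a property of the design: the likeliest observation in an arm, 0/12, leaves rates up to 26.5% open, and 1/12 leaves 0.2% to 38.5%. For the primary complications, only very large differences would be detected reliably (5% versus about 53% or 61%), and power for 10% versus 30% is 10% to 20%, depending on the test.

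The precision figures rest only on the article's inputs and 12 per arm. The power figures also rest on two-sided testing, the assumed rates, full follow-up and no adjustment for four primary outcomes. All take the 12 per group in Sample size calculation as intended. Materials and Methods can be read as 12 eligible patients in total, and with fewer than 12 per arm every figure would be worse.

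**What to change.** No extra patients are needed.

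- Keep the planned 12 per group, and reconcile it with Materials and Methods, which has 24 patients assessed and 12 meeting the criteria.
- Remove the 8% margin as the justification for N, and disclose that the Cochran calculation does not support the comparison. Give feasibility as the basis only if the sponsor confirms that it was.
- State what 12 per arm delivers at two-sided 5%, before dropout or multiplicity. For the primary complications: 80% power only for differences as large as 5% versus about 53% (uncorrected chi-square) or 61% (Fisher), and 10% to 20% power for 10% versus 30%, with the rates labelled as assumed. For a score compared by t test: 80% power only for about 1.20 SD, labelled approximate because the scales are ordinal.
- Report between-arm differences with 95% confidence intervals, using exact or small-sample methods for complications.
- Reword the Abstract, Utility, Expected outcome and Conclusion as exploratory. Present the p < 0.05 testing in Statistical analysis consistently with that, and say that a non-significant complication comparison does not show that the flaps are alike.

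The cost is one rewritten paragraph and several softened sentences. The downside is that the stated precision and the conclusions become less favourable.
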